**Pulmonary Function Testing**

- Chest and/or abdominal discomfort
- Vasovagal reaction
- Non-sustained hypotension
- Headache
- Sustained bronchospasm or chest tightness

**Hematology (Sickle Cell Anemia)**

- Anemia and its complications; chronic simple or exchange transfusion in transfusion program for anemia
- Transfusion reactions
- Treatable infections from bacteria, viruses, protozoa and fungi.
- Mild vaso-occlusive crisis requiring oral narcotic analgesia
- Vaso-occlusive crisis requiring hospital admission
- Avascular necrosis of the femoral head
- New leg ulcers

**Sildenafil**

- Transient minor headache
- Nasal congestion

- Dyspepsia
- Transient visual abnormalities including eyelid edema
- Asymptomatic hypotension

### **13.7.2 SAEs that Require Expedited Reporting to the IRB**

The following serious adverse events will be listed in the consent and reported to the local IRB within 7 days of a death or other life threatening event or 15 days of any other serious adverse event as outlined in the Interim Guidelines for Adverse Event Reporting. Other SAEs not noted herein will be reported to local IRBs per the guidelines of each IRB.

#### **Pulmonary Artery Catheterization**

- Conduction abnormalities or atrial/ventricular arrhythmias occurring during cardiac catheterization requiring pacing or cardioversion/defibrillation.
- Injury to coronary artery, myocardium, or great vessel during diagnostic or research cardiac catheterization that requires further treatment; interventionally, surgically or pharmacologically.
- Pericardial effusion following diagnostic/research cardiac catheterization study requiring more intensive monitoring, or treatment such as a pericardial tap.
- Pneumothorax following diagnostic/research cardiac catheterization (left ventricular puncture) requiring more intensive monitoring or insertion of a chest tube.
- Hematoma with pseudoaneurysm (of major artery resulting from inadvertent puncture or of the pulmonary artery) following the catheterization.
- Apnea requiring airway management during conscious sedation for diagnostic cardiac catheterization.
- Myocardial infarction/neurological event during or following (within 24 hours) diagnostic/research cardiac catheterization

#### **Hematology (Sickle Cell Anemia)**

- Priapism requiring medical or surgical intervention
- Acute chest syndrome/pneumonia requiring simple or exchange transfusion, admission and antibiotic therapy (not mechanical ventilation)
- Infections from bacteria, viruses, protozoa and fungi requiring vasopressor support or hospital admission
- Avascular necrosis of the femoral head requiring surgical intervention

- Bleeding requiring transfusion
- Major bleeding complication including intracerebral hemorrhage, stroke or GI bleed
- Sustained thrombocytopenia or neutropenia
- New leg ulcers requiring surgical intervention
- Greater than two admissions for vaso-occlusive crisis per week for two sequential weeks
- Retinal detachment or vitreous bleeding
- Pulmonary embolism
- All hospitalizations for medical indications (with the exception of hospitalizations for vaso-occlusive crises – per Section 13.7.1)

### **Pulmonary Function Testing**

- Sustained bronchospasm or chest tightness resulting in mechanical ventilation

### **Sildenafil**

- Hypotension requiring admission or fluid resuscitation
- Visual changes requiring discontinuation of therapy or ophthalmologic evaluation
- Hypotension that requires vasopressor support
- Priapism requiring exchange transfusion or surgical intervention

## **13.8 Reporting of Serious Safety Issues to the DSMB; Suspension Guidelines**

Serious safety issues that arise in this study will be brought to the attention of the Data and Safety Monitoring Board (DSMB), which will make recommendations to the National Heart, Lung, and Blood Institute (NHLBI) regarding possible suspension or termination of the study. The NHLBI will consider the DSMB's recommendations, determine an appropriate action and notify the Data Coordinating Center (DCC). The DCC will notify all participating investigators, who will implement the actions directed by the NHLBI. This section defines "serious safety issues" and describes procedures for bringing them to the attention of the DSMB.

The DCC or PI will make the following types of reports that can alert the DSMB to a potential safety issue:

- Ad hoc reports of unexpected serious adverse events and those serious adverse events associated with major bleeding that are made within 7 or 15 calendar days, as specified in subsequent paragraphs.

- Reports of quarterly statistical analyses of all serious adverse events. The DCC will make such analyses quarterly, but files a report to the DSMB only when analyses indicate that a safety issue has arisen, as defined by the “alert” criteria.
- Reports of semi-annual DCC analyses of all adverse events and of adverse clinical laboratory trends. These reports will highlight any safety issues revealed by the analyses that meet the “alert” criteria.

The DCC will submit the DSMB report to the Chair of the DSMB Subcommittee appointed to monitor this study and to the NHLBI Project Officer and will submit the unexpected SAE report to all study investigators. Each CI will submit the unexpected SAE report to the local Institutional Review Board (IRB) and other local authorities in accordance with the institution’s regulations.

### **13.8.1 Reporting of All Serious Adverse Events to the DSMB**

Three months after the first subject is enrolled in the study, and at the end of each 3 month period thereafter, if any SAEs (expected or unexpected) have been reported in the study during the preceding 3 months, the DCC will:

- Use the current version of the MedDRA dictionary to code all AEs (serious or not) that have been recorded on study AE forms.
- Make a “snapshot” copy of the adverse events data, including MedDRA codes.
- Create frequency tables of treatment x occurrence (yes or no, since inception of the study) of all subjects. One table will be created for each highest-level MedDRA term for which SAEs have been reported. The counting units are subjects, not events.
- Compute Fisher’s Exact Test (FET) statistic to test the alternative hypothesis that occurrence of SAEs is not independent of treatment group. The FET p-value is not adjusted for multiplicity.
- If the FET p-value is less than the critical value shown in Table 12 and the active treatment group has a higher AE rate, the DCC will conduct further statistical analyses as indicated by the circumstances and report the results to the Chair of the DSMB subcommittee monitoring this study, the PI, and the NHLBI Project Officer.

The DCC will not file a report of all SAEs if none of the FET p-values is less than the critical value shown in Table 12 or if the relative risk is less than 1.

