**Table 2. Inhaled NO and Oral Sildenafil Challenge at Baseline**

|        | Intervention     | Duration           | Assessment                 |
|--------|-------------------------|---------------------------|-----------------------------------|
| Step 1 | Baseline                |                           | Resting hemodynamics              |
| Step 2 | Inhaled NO 40 ppm       | 10 minutes                | Resting hemodynamics  |
| Step 3 | None                    | 10 minutes                | Resting hemodynamics              |
| Step 4 | Sildenafil 60 mg orally | 30 minutes post oral dose | Resting hemodynamics              |
| Step 5 |                         | 60 minutes post oral dose | Resting hemodynamics              |

 Resting hemodynamics assessed at the end of the 10 minute period of inhaled NO, while the subject is still inhaling the NO.

Right heart catheterization will be repeated at the end of the double-blind phase. This hemodynamic assessment will follow the guidelines below:

- Subjects will take their nighttime dose of study medication, but will not take their morning dose prior to right heart catheterization.
- Subjects will bring study medication to visit.
- Study medication is administered with direct observation by study coordinator
- Right heart catheterization will be performed approximately 4 hours after study medication is administered
- Baseline hemodynamic measurements will be performed as outlined in Table 2 (steps 1-3).
- Blinded study medication will be administered and hemodynamic measurements will be performed at 30 and 60 minutes post dosing as outlined in steps 4 and 5 of Table 2.

If during right heart catheterization, it is not possible to obtain an adequate reading of the pulmonary capillary wedge pressure, a left heart catheterization will be performed for the measurement of left ventricular end-diastolic pressure.

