#### **4.4.4 Open-Label Follow-up Phase**

After the completion of the 16-week randomized phase, patients will be offered open-label sildenafil for up to 1 year. Sites will maintain clinical outcome follow-up with these patients during this time, every 1-3 months, based on each site's standard practice. To preserve the scientific integrity of the MIT, all subjects will remain blinded to their MIT treatment assignment until after the MIT database is locked. In order to maintain the blind on a per subject basis and to minimize the possibility of sildenafil related adverse effects, at the beginning of the Open-label Follow-up Phase all patients will be down titrated from 80mg TID of sildenafil or placebo to 20 or 25mg of sildenafil TID. The doses will then be titrated upward as tolerated (see section 7.2 for dose adjustment guidelines in case of adverse effects). Doses will increase by 20-25mg TID every two weeks, but a faster dose escalation regimen will be allowed if, in the opinion of the treating clinician, a patient has become symptomatic due to apparent dose down-titration. The maximum dose will either be 75 mg or 80 mg TID, depending on 20 mg or 25 mg tablet availability. During the course of this year, the CI and administrative team will make every effort to assist patients in obtaining medication from a non-study source; this could include, for instance, helping obtain insurance coverage for their drug. Patients will be informed that these efforts do not guarantee availability of open label drug at the end of the study contract.

Adverse events and study drug dosing schedules will be collected during this open-label period.

If patients choose not to participate in the Open-Label Follow-up Study, they will be required to return to the clinic for a one-month safety follow-up visit approximately 30 days after the MIT Week 16 visit. Clinical Investigators will taper study drug for these non-continuing patients upon completion of the MIT treatment phase. The taper will continue for 3-7 days, based on CI judgment; blinded study medication will be provided in a quantity sufficient to supply the maximum taper period. Tapering is not recommended for patients requiring discontinuation of the drug due to AEs.

Refer to Chapter 13.3 of the MOO for a suggested taper regimen and for additional details.

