## **11 STATISTICAL METHODS**

### **11.1 Analysis Populations**

This study is designed to enroll sickle cell disease subjects diagnosed with PH.

*Intent-to-Treat (ITT) / Safety population (SAF):* All randomized subjects will be included in the ITT/SAF population. Subjects in the ITT/SAF population will be classified according to the treatment group to which they were randomized, regardless of what study drug they received.

*Per-Protocol (PP) population:* The PP population consists of all subjects from the ITT/SAF population who had no major protocol violations and who were followed until discharge from the study.

The primary efficacy analysis will be an intention-to-treat analysis. Secondary analyses of efficacy and safety will be performed on the ITT/SAF population, and many of the secondary efficacy analyses will be repeated on the PP population.

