### **11.3 Safety Analyses**

All safety analyses will be performed using the ITT/SAF population. Safety variables will include laboratory variables and adverse event information. Specific endpoints that will be examined include:

- Incidence of AEs between baseline and Week 16
- Incidence of SAEs between baseline and Week 16
- Mortality incidence

The primary safety outcomes for the MIT will be all AEs; the subset of AEs defined as SAEs; and mortality. Treatment emergent AEs (those that begin or worsen after start of study drug), drug-related AEs, SAEs, and drug-related SAEs (as determined by the investigator) will be categorized by body system and MedDRA (Version 6.0 or later) preferred term.

The assessment of safety data will be based mainly on the tabulation of AEs, by TRV stratum and treatment arm. Additionally, AEs will be tabulated by severity and relationship to drug. Serious AEs will be described in detail. Comparisons across treatment groups, stratifying on TRV stratum will be made using a Cochran-Mantel-Haenszel chi-square test (or Fisher's Exact test as appropriate) on any AEs that occur in more than 10% of the subjects.

Additionally, continuous blood chemistry and hematology laboratory measurements will be categorized as normal/abnormal and summarized using shift tables, which describe changes in the values across visits.

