### **13.5 Reporting of Adverse Events**

In the screening phase, AEs will be reported if they begin or worsen from the time a subject signs informed consent for the Screening phase through 7 days after the last screening procedure and only if the investigator believes the event to be possibly associated with that study procedure.

In the MIT and Open-label follow-up phases, the study will capture AEs that begin or worsen in the period from provision of MIT informed consent through the either the last dose of study drug OR until discontinuation from the MIT (for those consented subjects who were never treated).

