|-------------------------------------------|------------------------------------------------------------------------------------------------------------------------------------------------------------------------------------------------------------------------------------------------------------------------------------------------------------------------------------------------------|--------------------------------------------------|
| Unexpected SAEs                           | Clinical investigator notifies DCC SAE Regulatory Specialist and PI.
Clinical investigator, DCC SAE Regulatory Specialist and PI prepare report using FDA forms and submit report to DSMB, NHLBI Project Officer, IRBs, study investigators. Report:
Fatal or life-threatening: within 7 calendar days.
Otherwise: within 15 calendar days. | Alert all cases.                                 |
| Serious Bleeding Events, other than above | Clinical investigator notifies DCC SAE Regulatory Specialist and PI.
Clinical investigator, DCC SAE Regulatory Specialist and PI prepare report and submit report to DSMB and NHLBI Project Officer within 15 calendar days                                                                                                                       | Alert all cases.                                 |
| All SAEs                                  | DCC performs quarterly analyses of MedDRA-coded SAEs, tabulates subjects with SAEs classified by highest-level MedDRA term. Report only when $p <$ critical value and active treatment group has higher AE rate.                                                                                                                                     | $p < 0.01$
$p$ not adjusted for multiplicity  |
| Adverse Events (all)                      | DCC performs semi-annual analyses of MedDRA-coded AEs, tabulates subjects with AEs classified by highest-level MedDRA term. Report every 6 months. Alert only when FET $p <$ critical value and active treatment group has higher AE rate.                                                                                                           | $p < 0.01$
$p$ not adjusted for multiplicity  |

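### The AE and SAE alert tables for the DSMB have no cut-off at the end of the double-blind phase, so open-label sildenafil events in placebo-randomised subjects count as placebo events and blunt the p<0.01 alert

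*Protocol*

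**What the plan says.** Protocol 13.8.1 (SAEs, quarterly) and 13.8.2 (all AEs, every six months) use the same instruction: "Create frequency tables of treatment x occurrence (yes or no, since inception of the study) of all subjects". There is one table per highest-level MedDRA term, and subjects are counted, not events. Fisher's exact test is then used, in 13.8.1 "to test the alternative hypothesis that occurrence of SAEs is not independent of treatment group". An alert needs an unadjusted p below 0.01 and a higher rate on active treatment (Table 12). If no SAE table meets this, no quarterly SAE report is filed.

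Four other places determine what enters the table:

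- **Collection.** Under 13.5, for the main trial and the open-label phase together, "the study will capture AEs that begin or worsen in the period from provision of MIT informed consent", continuing to the last dose of study drug. Section 13.6 runs SAE reporting to one month after the last dose.
- **Crossover.** Section 4.4.4: "After the completion of the 16-week randomized phase, patients will be offered open-label sildenafil for up to 1 year". This applies to both arms.
- **Attribution.** Section 11.1: ITT/safety subjects are "classified according to the treatment group to which they were randomized, regardless of what study drug they received".
- **Pre-randomisation exposure.** Subjects with TRV of at least 3.0 m/s, planned as half of the trial, undergo the Table 2 challenge ("Sildenafil 60 mg orally") before they are randomised.

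The final safety analysis in 11.3 does have a window, for example "Incidence of AEs between baseline and Week 16". Section 13.8 does not carry that limit over.

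**The concern.** The alert compares arms, so it can detect harm only while the arms differ in exposure. After Week 16 they no longer do, because completers of both arms may take sildenafil. A table that accumulates from study start and never closes keeps adding events at the sildenafil rate to the placebo row, for up to 52 weeks after only 16 weeks of placebo. A true toxicity then appears as two high and similar rates.

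Recruitment is expected to take about 13 months. Early entrants are therefore on open-label drug while others are still being randomised and escalated, so the dilution begins while the alert could still protect subjects in the double-blind phase.

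**Working it through.** **1. Denominators.** A noncentral-t calculation with a 40 m difference, SD 67 m, two-sided 0.05 and 90% power gives 60 per arm, as in Table 6. Then 60 × 1.10 = 66 per arm, 132 in total, as section 11.6 states. The protocol gives no power for the safety alert. With 66 per arm and no placebo events, 8 sildenafil events are needed (p = 0.006; 7 give p = 0.013).

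**2. Dilution for one subject pair.** The protocol gives no event rates for this population, so 16-week risks of 25% (sildenafil) and 5% (placebo) are assumed, with constant hazards.

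- Sildenafil hazard: −ln(0.75)/16 = 0.01798 per week.
- Placebo hazard: −ln(0.95)/16 = 0.00321 per week.
- After 52 open-label weeks, sildenafil row: 1 − exp(−68 × 0.01798) = 71%.
- After 52 open-label weeks, placebo row: 1 − exp(−(16 × 0.00321 + 52 × 0.01798)) = 63%.

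A 20-point contrast (25% against 5%) becomes an 8-point contrast (71% against 63%).

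**3. Power of the alert.** Simulation with 66 per arm, uniform entry over 13 months, 16 double-blind weeks, then 52 open-label weeks for everyone. The criterion is two-sided Fisher p<0.01 with the sildenafil rate higher, and subjects are attributed as randomised.

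| Look | Double-blind events only | As written |
|---|---|---|
| Month 6 | 12% | 9% |
| Month 9 | 36% | 14% |
| Month 12 | 57% | 14% |
| Month 15 | 69% | 12% |
| Any quarterly look | 75% | 34% |

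Repeat runs agree within about 4 points. With 80% open-label uptake and 26 open-label weeks, the any-look figures are 77% and 41%.

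**4. Other assumed rates.** Chance of an alert at any quarterly look (full uptake and 52 weeks; in brackets, 80% uptake and 26 weeks):

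| Placebo 16-week risk, hazard ratio | Double-blind only | As written |
|---|---|---|
| 5%, 3 | 17% | 10% (10%) |
| 5%, 5 | 66% | 27% (34%) |
| 10%, 3 | 48% | 25% (25%) |
| 10%, 4 | 80% | 40% (45%) |
| 20%, 3 | 83% | 42% (47%) |

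With a 2% placebo risk and a hazard ratio of 2 to 3, the clean table has only about 1% power at a look with all subjects complete, so there is almost nothing to lose.

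**5. The baseline challenge alone.** It is a single dose in about half of each arm. A 1% event risk costs about 1 to 2 points of power, 5% about 6 to 12, and 15% about 22 to 26. The documents give no event risk for the challenge.

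**The case against.** **Other safety routes exist.** This stands. Table 12 requires every unexpected SAE and every serious bleeding event to be reported without a test. The all-AE report goes to the DSMB every six months whatever the p-value; the 0.01 limit only decides what is flagged in it. Laboratory trends have their own test at p<0.005, and Table 4 schedules no open-label laboratory tests. The DSMB also receives a safety report before each meeting (13.10.1). A reader might infer that the Fisher table is the only statistical trigger, or that nothing would reach the DSMB without it; the protocol does not support either. The gap is narrower. Table 11 lists acute chest syndrome and vaso-occlusive pain as expected, and an excess of such SAEs prompts a quarterly report only through this table. The flag in the semi-annual AE report uses a table built the same way.

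**Section 13.8 does not define treatment.** This is true: as-randomised attribution comes from 11.1 and is an inference, though the natural one. Classifying by current drug does not rescue the table. The counting unit is the subject, and a placebo subject who crosses over would belong in both rows of a test that needs independent groups.

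**The loss depends on the look chosen.** Also true. One might conclude from a late look that the alert loses most of its power: at month 18 the figures are 70% against 8%. But the last randomised subject finishes at about month 17 (13 months plus 16 weeks), so such looks say nothing about protecting subjects during double-blind dosing. Month 6 is almost unaffected. For a rule applied every quarter, the any-look probability is the fair summary. Full uptake is also an upper case, because open-label entry is optional and early discontinuation bars it (7.1).

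**The 60 mg challenge.** It is tempting to say that its events are charged to placebo. They are not: it precedes randomisation and falls equally on both arms, so it dilutes the contrast without favouring either arm.

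**Section 11.3.** Its baseline-to-Week-16 wording might seem to share the fault. That section also defines treatment-emergent AEs as those starting or worsening after study drug begins, which already separates challenge events.

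**Conclusion.** The point holds for the AE and SAE alert tables in 13.8.1 and 13.8.2. They have no end of window, and read with 11.1 they place open-label sildenafil events of placebo-randomised subjects in the placebo row. Under assumed 16-week rates of 25% and 5%, the chance of any quarterly alert falls by about half (75% to 34%, or 77% to 41% with partial uptake). The loss is slight at month 6 and large at single looks from month 9. In the other scenarios tried, the relative loss is about 40 to 60%. All these figures rest on assumed event rates, constant hazards and assumed open-label uptake; for rare events the clean table is also weak. Given the remaining reporting routes and the simple remedy, this should be fixed but does not invalidate the monitoring plan.

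**What to change.** In 13.8.1 and 13.8.2, replace the since-inception window. Limit the arm comparison, by randomised arm, to events with onset after the first randomised dose and before the first open-label dose. For subjects who do not enter open label, run it to the end of the AE or SAE capture window in 13.5 and 13.6.

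Add two descriptive tables without an arm comparison: one for events from main-trial consent to the first randomised dose (including the catheterisation challenge), and one for open-label events.

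No change to 11.3 is needed.

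Cost: a date filter on data already collected and two extra descriptive tables per report. No safety information is lost.

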RhoRAND will be configured to send alerts to the project administrative team when numbers in a stratum approach 66. Based on power calculations, a minimum of 64 subjects with  $TRV \geq 3.0$  m/s should be randomized. Additionally, slight over-enrollment in the  $2.7 \text{ m/s} \leq TRV < 3.0 \text{ m/s}$  stratum may be permitted by NHLBI, if funding is available at that time.

To preserve the scientific integrity of the MIT, all subjects will remain blinded to their MIT treatment assignment until after the MIT database is locked.

Pharmacists at each site will be blinded and will utilize the blinded randomization notification from RhoRAND to issue appropriate study drug to each randomized subject. The RhoRAND system is able to provide unblinding information in case of a medical emergency where the exact study drug is needed in order to appropriately treat a subject. This information can only be accessed by a pre-authorized individual, such as the medical monitor.

The subjects, physicians, nurses, and ancillary support staff will be blinded to individual treatment assignment. The placebo formulations will be identical in appearance and taste to the active compounds (see Section 8.1).

The mechanism for unblinding in a clinical emergency will be detailed in the Manual of Operations.

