### **13.8.2 Reporting of All Adverse Events (Serious and Non-serious)**

Six months after the first subject is enrolled in the study, and at the end of each 6 month period thereafter, the DCC will:

- Use the current version of the Medical Dictionary for Regulatory Activities (MedDRA) to code all AEs that have been recorded on study AE forms.
- Make a “snapshot” copy of the adverse events data, including MedDRA codes.

- Create frequency tables of treatment x occurrence (yes or no, since inception of the study) of all subjects. One table will be created for each highest-level MedDRA term for which AEs have been reported. The counting units are subjects, not events.
- Compute Fisher's Exact Test (FET) statistic to test the alternative hypothesis that occurrence of AEs is not independent of treatment group. The FET p-value is not adjusted for multiplicity.
- If the FET p-value is less than the critical value shown in Table 12 and the active treatment group has a higher AE rate, the DCC will conduct further statistical analyses as indicated by the circumstances and alert the DSMB to this finding in the semi-annual DSMB report.
- Collaborate with the PI to incorporate the results into the study's semi-annual report to the DSMB and the NHLBI Project Officer.
- A copy of the study's semi-annual report will be submitted to the IND Holder's IRB. Measures will be taken to ensure that the PI and Study Coordinator at that site remain blinded to their subject's treatment.

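### The PI is brought into by-arm interim safety and laboratory results every six months, and the blinding statements protect only individual treatment assignment

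*Protocol*

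**What the plan says.** **Semi-annual route, no condition.** Under section 13.8.2 the DCC tabulates all adverse events by treatment and runs Fisher's exact test between arms every six months. Section 13.8.3 does the same for laboratory change from baseline, testing whether the active group is worse. In both sections the DCC must then "Collaborate with the PI to incorporate the results into" the semi-annual report, which goes to the DSMB and the NHLBI Project Officer. An alert adds further analysis and a flag. It does not decide whether the PI takes part.

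**Quarterly route, conditional.** Section 13.8.1 starts from cumulative tables: "Create frequency tables of treatment x occurrence (yes or no, since inception of the study) of all subjects". The trigger reads "If the FET p-value is less than the critical value shown in Table 12 and the active treatment group has a higher AE rate", and the DCC will then "report the results to the Chair of the DSMB subcommittee monitoring this study, the PI, and the NHLBI Project Officer". Otherwise nothing is sent: "The DCC will not file a report of all SAEs if none of the FET p-values is less than the critical value". Table 12 agrees ("Report only when $p <$ critical value and active treatment group has higher AE rate") and sets the critical value at 0.01, unadjusted.

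**Blinding.** Section 6 states: "The subjects, physicians, nurses, and ancillary support staff will be blinded to individual treatment assignment". Section 13.8.2, when it provides for a copy to the IND Holder's IRB, adds "Measures will be taken to ensure that the PI and Study Coordinator at that site remain blinded", with reference to their own subject's treatment. The matching sentence in 13.8.3 names the CI in place of the PI. Section 6 also mentions an unmasked statistician, whose only stated task is to watch the balance of anticoagulant use.

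**The concern.** In a double-blind trial, those who lead its conduct should not see comparative interim data, even aggregated. Here the PI is written into the preparation of those data, and no sentence on blinding reaches group-level results. Coding the arms would not fully close the gap, because the SAE alert rule and the laboratory alternative hypothesis both name the active group as the worse one.

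What is at stake is trial conduct. Several decisions that feed the primary endpoint are discretionary:

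- Section 7.1 lets an investigator withdraw a subject on clinical judgement.
- Section 7.2 leaves it to the subject or physician whether headache or edema is severe enough to hold drug.
- Under section 11.5.5, stopping for clinical worsening without an end-of-study walk leads to imputation of the worst value in that arm and stratum.

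Someone who knows the safety trend by arm could influence such decisions through advice to sites, without intending to.

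**Working it through.** The plan gives no figure for the number of disclosures, so there is none to reproduce. The sample size in section 11.6 is not affected.

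**1. Who sees what**

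| Section | By-arm content | PI involved? | Condition |
|---|---|---|---|
| 13.8.1 | SAEs, quarterly | Receives results | p < 0.01 and active arm worse |
| 13.8.2 | All AEs, semi-annual | Helps incorporate results | None |
| 13.8.3 | Laboratory change, semi-annual | Helps incorporate results | None |

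**2. What the safeguards cover**

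| Section | Who stays blinded | To what |
|---|---|---|
| 6 | Subjects, physicians, nurses, support staff | Individual assignment |
| 13.8.2 | PI and coordinator at one site | Their subject's treatment |
| 13.8.3 | CI and coordinator at one site | Their subject's treatment |

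No row of the second table covers the content in the first. The two also conflict over the PI: 13.8.2 treats the PI as someone with subjects to stay blinded to, yet also has the PI work on by-arm results.

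**3. Number of review points before the last Week 16 visit**

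Inputs: recruitment of about 13 months (section 4.1), 16 weeks of treatment, and a first review 3 or 6 months after the first subject is enrolled.

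- Span: 13 + (16 × 7)/30.4375 = 13 + 3.68 = 16.7 months.
- Semi-annual: 16.7/6 = 2.8, so 2 reports (months 6 and 12).
- Quarterly: 16.7/3 = 5.6, so 5 SAE analyses (months 3 to 15).

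The two semi-annual reports are the routine exposure. The five quarterly analyses stay inside the DCC unless an alert is met.

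**4. How likely is a quarterly disclosure?**

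Method: exact binomial enumeration of Fisher's two-sided test, counting outcomes with p < 0.01 and the active arm higher. The event rates are assumptions, because the protocol gives none for these terms.

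| Per arm | True rate, both arms | Chance of alert, one term, one analysis |
|---|---|---|
| 33 | 10% | 0.06% |
| 33 | 20% | 0.18% |
| 66 | 10% | 0.23% |
| 66 | 20% | 0.27% |

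With equal arms and no true difference, the chance in one direction cannot exceed 0.01/2 = 0.5% per term per analysis. Five analyses therefore give at most 5 × 0.5% = 2.5% per term. The chance over all terms rises with the number of terms that have SAEs, which the protocol cannot state in advance.

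At 66 per arm, the smallest splits (active v placebo) that trigger a report are 8 v 0, 12 v 2, 17 v 5 and 24 v 10. If a report does reach the PI, it therefore shows a marked imbalance against sildenafil.

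**The case against.** **Exposure may look larger than it is.** A reader might count five quarterly plus two semi-annual analyses as seven unblinded looks. The text does not support this, because SAE results leave the DCC only after an alert. This objection stands, and the point therefore rests on 13.8.2 and 13.8.3.

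**Symptoms may seem to label the arms.** A reader might take the Table 8 rates (headache 16% v 4%, flushing 10% v 1%) as proof that the arms could be recognised. At those rates the alert probability at 66 per arm would be about 31% and 22%. But the monitoring tables use the highest-level MedDRA term, which pools each symptom with many other events. The rates also come from as-needed use in other patients. They do not show what these tables would display, and the point does not need them.

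**Bias in the walk distance may be inferred.** The documents do not show it. No walk result is reported and no formal interim analysis is planned (section 11.4). The walk is scripted and unencouraged (Appendix D), and a blinded panel adjudicates clinical deterioration of PH (section 9.2.4). Titration is scheduled, and the primary model, covariates, alpha and imputation rules are already written down. No section sends these tables to walk testers. What remains is an indirect route through discretionary conduct.

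**Who the PI is.** The protocol uses both PI and CI, defines only CI in its abbreviations, and has the DCC or the PI make these reports (section 13.8). Whether this PI treats or assesses subjects is not stated. That lowers certainty about the consequence, but it is itself an ambiguity to settle.

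**The Project Officer and the DSMB charter.** NHLBI holds the IND and decides on suspension, so alerting its Project Officer may be deliberate. That is a fair defence, and exclusion of that officer is not required here. The charter mentioned in section 13.10.1 is not shown and might split open from closed reports. If it does, sections 13.8.2 and 13.8.3 still say otherwise and need to be aligned with it.

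**Conclusion.** The concern holds in a limited form. As written, the plan involves the PI in between-arm adverse event and laboratory results about twice before the last Week 16 visit. It also sends by-arm SAE results to the PI if an alert occurs. Nothing in the document protects aggregate by-arm results, and the one sentence that comes close names the PI in one section and the CI in the other.

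The count of two assumes that recruitment takes the planned 13 months; slower accrual would add reports. The conclusion also assumes that the results to be incorporated are the between-arm ones just described, which is the natural reading.

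The exposure is to aggregate safety and laboratory data. Its effect on the primary endpoint is indirect and cannot be quantified from the protocol. This is a cheap improvement worth making, not a defect that invalidates the design.

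**What to change.** 1. In 13.8.1 to 13.8.3 and Table 12, have the unmasked statistician named in section 6 prepare all by-arm tables in a closed report for the DSMB.
2. Remove the PI from the by-arm steps in those three sections. Give the PI an open report pooled over arms, together with the DSMB's recommendation.
3. Extend the blinding statement in section 6 to aggregate by-arm results until database lock.
4. Reconcile PI and CI in the safeguard sentences of 13.8.2 and 13.8.3, and define PI.
5. If the NHLBI Project Officer must receive by-arm alerts for the suspension decision, state that this person is kept apart from trial conduct and enrolment decisions. One such decision is NHLBI's option in section 6 to permit over-enrolment in the lower TRV stratum.

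Case-level reports of unexpected SAEs and serious bleeding can stay as written. The cost is revised wording and two versions of each report, with no new data. The downside is that the PI learns of a by-arm safety signal only through the DSMB or NHLBI.
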